### Sample size and power analysis

The sample size estimation was conducted using Power Analysis and Sample Size (PASS) software (version 15, PASS, NCSS, LLC). The calculations were based on detecting a small effect size (Cohen’s d = 0.20) in the business advisors primary outcome quality of the relationship as measured from an amended Relationship Flourishing Scale [24]. A sample of 786 business advisors randomly allocated (1:1) to the two study arms will achieve 80% power to detect an effect size d = 0.2 in the primary outcome or a mean difference of 1.52 between the two groups. The mean difference of 1.52 was calculated using the results from a validation study of the Relationship Flourishing Scale on 408 participants who reported a mean score of 46.36 and standard deviation of 7.60 [24]. Assuming a 20% attrition rate, we will recruit 984 business advisors. Calculations are based on a two-tailed test and α = 0.05.

### Statistics

A report of the findings will follow CONSORT guidelines. The quantitative analysis will examine whether the magnitude of change in primary and secondary outcomes is different between the SME owners and their business advisors randomly allocated to the MFHA or RBT + MHFA arm (i.e., between-group differential change). Population average models, using a generalised estimated equation (GEE) approach accounting for within-individual repeated measures, will be used to assess for a treatment effect in the primary outcome. The analysis will employ an unstructured correlation structure for the GEE analysis and include a robust covariance matrix estimator, or Sandwich estimator, to provide a consistent estimate of the treatment effect. The GEE approach models the average response of the population rather than modelling the within-subject covariance structure, and unlike a basic regression model, it does not require distributional assumptions. It considers the correlation of within-subject data (longitudinal data) by using all available data for each subject, and it can be used on data with non-normal distributions. The GEE model will contain the fixed effect of intervention allocation and nominal time points as the main effects, and a two-way interaction between intervention allocation and time. The two-way interaction will estimate the effect of differential change from baseline measure in the intervention compared with control group at 2- and 6-months measurements. The GEE model will compare the between-group mean change for business advisors from baseline to 2-months (1-month post-training), baseline to 6-months (4 months post-training), 2-months to 6-months to test the hypothesis (i.e., the two-way interaction between intervention allocation and measurement at 2-months and it’s 95% confidence interval). For SME owners, the between-group differential change will be assessed from baseline to 6-months, baseline to 12-months, and 6-months to 12-months.

In unblinded randomised control trials, participants allocated to the control group who are aware of a more desirable treatment group, may be envious of participants in the treatment group and be less willing to complete surveys [38, 39]. Because of the appeal the new RBT may offer to business advisors, we anticipate that participants in our MHFA alone group may be unmotivated to attend training sessions, complete surveys and ultimately dropout. If such a trend is observed in this study, we may take a pragmatic decision to change the random allocation ratio to allocate more participants to MHFA alone to have equal number of participants in both groups to enhance statistical power. If such a change in the allocation ratio is needed (e.g., from 1:1 to 1:2 to account for differential attrition), the participants will no longer have an equal chance of receiving each of the treatments. Bias could also arise if participants differ in important characteristics, hence the data from these two parts of the trial will be tested for homogeneity. If any significant differences are identified, the results will be analysed separately and then combined, as in a meta-analysis [40].

All analyses will be tested with a significance level of *p* < 0.05 by using the intention to treat principle. Participants classified as lost to follow-up will be compared with the study group for baseline demographic data using ordinary t test and χ2 test for homogeneity. A sensitivity analysis will be conducted to investigate the impact of dropouts on our primary hypothesis. Magnitude of change will be estimated through effect sizes using Cohen’s guidelines, whereby a value of 0.2 denotes a small, 0.5 a medium, and 0.8 a large effect size [41–43]. Data will be entered into Excel using Microsoft Office (version 16.0.1). Professional for Windows XP and StataSE (version 16) software for statistical analysis.

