**Methods:**

This is a single blind, two-arm randomised controlled trial. Participants will be business advisors who provide information, guidance and/or assistance to SME owner clients and are in contact with them at least 3 times a year. The business advisors will invite their SME-owner clients to complete 3 online surveys at baseline, 6- and 12-months. Business advisors will be randomised to one of two conditions, using a 1:1 allocation ratio: (1) MHFA with RBT; or (2) MHFA alone, and complete 3 online surveys at baseline, 2- and 6-months. Primary outcomes will be measured in the business advisors and consist of the quality of the relationship, stigmatizing attitude, confidence to offer mental health first aid, quality of life and provision of mental health first aid. Secondary outcomes will be measured in the SME owners and includes trust in their business advisors, the quality of this relationship, financial wellbeing, financial distress, psychological distress, help-seeking behaviour, and quality of life. To complement the quantitative data, we will include a qualitative process evaluation to examine what contextual factors impacted the reach, effectiveness, adoption, implementation, and maintenance of the training.

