#### SME owners

Business advisors will be asked to invite their SME owner clients to take part in the study to help assess the effectiveness of the training from the perspective of someone who is expected to benefit from it. The SME owner clients will complete 3 online surveys at baseline, 6 and 12 months (or 5- and 11 months follow-up post-training). Business advisors will be requested to send a pre-prepared email to 2–5 of their SME owner clients inviting them to participate (Figs. 1 and 2). However, this is not a mandatory requirement for business advisors.

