### Process evaluation

The second aim of this project is to undertake a comprehensive, research-to-practice process evaluation to ensure that the assessment of Counting on U extends beyond the effectiveness of the interventions [36, 37]. We will draw on the research translation evaluation framework, RE-AIM (i.e., Reach, Effectiveness, Adoption, Implementation, and Maintenance), to explore: the processes used to Reach a nationally representative sample of practising business advisors; how Effective and relevant the intervention is to business advisors and SME owners, and what factors helped or hindered the business advisors to apply what they learnt; what factors influenced the professional member bodies to Adopt the training; whether the instructors Implemented the training in the way it was intended, and; why or why not the professional member bodies decide to Maintain the training as part of their ongoing career professional development program and whether any benefits of the training are Maintained long-term.

To measure these outcomes, field notes and qualitative structured interviews via zoom will be conducted during the training with the business advisors, SME owners, instructors, training vendors, and professional member organization representatives who will assist with the recruitment of business advisors. A risk mitigation-strategy will be designed for the researchers to use in case any interviewee is experiencing poor mental health. To assess intervention fidelity (Implementation), the research team will observe training sessions and complete a fidelity checklist to ensure all topics are covered and that the quality of the teaching is meeting expectations. The research team will observe all 14 instructors deliver the five training sessions (i.e., 1 x RBT, 2 x MHFA, 2 x Booster). The training program will also be monitored through regular weekly meetings between the research team, the instructors, and the training vendor.

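### SME-owner outcomes: the only model described clusters on the person, although the advisor was randomised and several clients may share one advisor

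*Protocol article*

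**What the plan says.** The randomised unit is the advisor. The Methods paragraph of the abstract states that "Business advisors will be randomised to one of two conditions, using a 1:1 allocation ratio", and the Randomisation section agrees. Clients enter through their advisor. Under Recruitment, SME owners, "Business advisors will be requested to send a pre-prepared email to 2–5 of their SME owner clients inviting them to participate", and the article adds that this is optional. All clients of one advisor therefore share that advisor's allocation.

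The Statistics section opens by promising a comparison of change in primary and secondary outcomes, for owners and for advisors. The model it then describes is "Population average models, using a generalised estimated equation (GEE) approach accounting for within-individual repeated measures". That sentence goes on to refer to the primary outcome, which the Measures section assigns to advisors. Further on, "The analysis will employ an unstructured correlation structure for the GEE analysis and include a robust covariance matrix estimator, or Sandwich estimator", and of the method in general, "It considers the correlation of within-subject data (longitudinal data) by using all available data for each subject". On the terms: "The GEE model will contain the fixed effect of intervention allocation and nominal time points as the main effects, and a two-way interaction" between arm and time. The paragraph closes with the owners: "For SME owners, the between-group differential change will be assessed from baseline to 6-months, baseline to 12-months, and 6-months to 12-months". No other model is given for owners. The article mentions no advisor level, intracluster correlation or design effect.

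**The concern.** For owner outcomes this is a cluster-randomised comparison in which the advisor is the cluster. A GEE treats its declared clusters as independent of one another. If the declared cluster is the owner, two clients of one advisor count as two independent observations of the arm effect.

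The robust variance does not help. It protects against a wrong working correlation inside the declared cluster, here one owner's three surveys. It does not protect against correlation between declared clusters.

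Some correlation is plausible. Two of the owner outcomes, trust and relationship quality, are ratings of the shared advisor. If advisors differ in how well they apply the training, their clients' changes will tend to move together. The owner outcomes also carry the aim stated in the abstract, which concerns the financial and mental health of clients. Overstated precision there would bear directly on the trial's claim of client benefit.

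**Working it through.** **1. The plan's own figure.** Sample size and power analysis gives a difference of 1.52, SD 7.60, two-sided α = 0.05 and 80% power.
- n per arm = 2 × (1.960 + 0.842)² × (7.60/1.52)² = 2 × 7.85 × 25 ≈ 392.5, so 393 per arm and 786 in total, as stated.
- With 20% attrition: 393/0.8 = 491.25, so 492 per arm and 984 in total, as stated.

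The calculation concerns an advisor outcome and treats individually randomised advisors as independent. It reproduces. The article gives no corresponding calculation for owners.

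**2. Which correlation matters.** Write the outcome of client j of advisor i at time t as a stable advisor effect aᵢ, plus a time-varying advisor effect bᵢₜ, plus client-level terms. The tested quantity is the arm-by-time interaction, a difference in change. In a change score aᵢ cancels and bᵢₜ − bᵢ₀ remains. The relevant intracluster correlation is therefore

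ICC = Var(bᵢₜ − bᵢ₀) / Var(change).

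It is the ICC of change. The ICC of the level at one survey may be larger.

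**3. Formulae.** Let m be the number of participating clients per advisor, taken as equal across advisors.
- Design effect: DE = 1 + (m − 1) × ICC
- Reported SE / true SE = 1/√DE
- Actual two-sided error of a nominal 5% test = 2 × [1 − Φ(1.96/√DE)]

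Example with m = 3 and ICC = 0.10: DE = 1 + 2 × 0.10 = 1.20; 1/√1.20 = 0.913; 1.96/√1.20 = 1.789; error = 2 × [1 − Φ(1.789)] = 7.4%.

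**4. Results.** The values of m span the number of clients an advisor is asked to invite; how many take part is not stated. The ICC values are assumptions, because the article gives none.

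| m | ICC of change | DE | SE ratio | Actual error |
|---|---|---|---|---|
| 2 | 0.05 | 1.05 | 0.976 | 5.6% |
| 2 | 0.10 | 1.10 | 0.953 | 6.2% |
| 2 | 0.20 | 1.20 | 0.913 | 7.4% |
| 3 | 0.05 | 1.10 | 0.953 | 6.2% |
| 3 | 0.10 | 1.20 | 0.913 | 7.4% |
| 3 | 0.20 | 1.40 | 0.845 | 9.8% |
| 5 | 0.05 | 1.20 | 0.913 | 7.4% |
| 5 | 0.10 | 1.40 | 0.845 | 9.8% |
| 5 | 0.20 | 1.80 | 0.745 | 14.4% |

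The shortfall in the SE runs from 1 − 1/√1.05 = 2.4% to 1 − 1/√1.80 = 25.5%. With m = 1 or ICC = 0, DE = 1 and nothing changes.

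**5. Check by simulation.** Client change scores were simulated under no treatment effect, with 200 advisors per arm (assumed) and 4,000 replications. Rejection at nominal 5%:

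| m | ICC of change | Individual-level variance | Advisor-level variance |
|---|---|---|---|
| 3 | 0.05 | 6.3% | 5.3% |
| 3 | 0.10 | 7.3% | 5.1% |
| 5 | 0.10 | 9.4% | 4.8% |
| 5 | 0.20 | 14.4% | 5.0% |

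The simulation agrees with the formula, and clustering on the advisor restores the nominal level.

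**The case against.** **The GEE sentence is about the primary outcome.** This is correct. For advisors the individual is the randomised unit, so within-person clustering is the right level there. The use of the same model for owners is read from the paragraph as a whole. That reading is fair: the section opens with both outcome sets and both populations, ends with the owner contrasts and offers no other model. An analysis plan not shown here may name the advisor as the cluster. Even so, the article states which correlation is handled, and for owners that level is too low.

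**Few clients per advisor may take part.** This also stands. Inviting clients is optional, and the Discussion expects owner recruitment to be difficult. An average of 3.5, the midpoint of 2 to 5, would mean close to full uptake. The lower rows of the table may be nearer the truth.

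**Stable advisor differences cancel.** They do, as step 2 shows. That some advisors are always more trusted is not enough; their clients' changes must be correlated. A reader might infer that every owner interval is certainly too narrow. The article does not support that, because it gives no ICC for any outcome.

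**A reader might extend the point to the advisors' own outcomes**, since training is live and shared among instructors: "The research team will observe all 14 instructors deliver the five training sessions". That sentence describes fidelity monitoring. The article states neither session size nor any correlation within sessions, and does not say that sessions or instructors are nested within arm. An instructor effect common to both arms would largely cancel. There is no basis here for calling the advisor p-values or the 80% power wrong.

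**Conclusion.** The point holds for the SME-owner secondary outcomes only. As written, the plan accounts for correlation within an owner and not between owners who share a randomised advisor. The direction is certain whenever the ICC of change is above zero and advisors contribute more than one client: intervals too narrow, type I error above 5%.

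The size is conditional. Over the assumed range it goes from negligible (5.6% at two clients, ICC 0.05) to serious (14.4% at five clients, ICC 0.20). Where the trial will fall depends on two quantities that the article does not give. The individual-level GEE for the advisors' primary outcomes stands, as do the 786 and 984.

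**What to change.** For SME-owner outcomes, state that the advisor is the independent unit, and amend the within-individual wording accordingly. Either of these will do:
- a GEE in which all clients and occasions of one advisor form one cluster, with an independence or exchangeable working correlation and the sandwich SE clustered on the advisor;
- a mixed model with random effects for advisor and owner.

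The unstructured working correlation should not simply be carried over to these larger clusters, because clients of one advisor have no natural order.

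Confirm that each client record is linked to its advisor's ID. The Randomisation section says that participants use a unique ID for their surveys, but not that client records carry the advisor's ID. Recruitment was ongoing at publication, so this is best settled early; a missing link may be hard to recover later.

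The cost is a few sentences, a model option and the linkage check, with somewhat wider owner intervals if the correlation is real. Allowing for training group in the advisor analysis is at most an optional sensitivity analysis.

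### The 80% power is computed for a comparison of raw scores at one time point, but the planned test is an unadjusted difference in change from baseline, so the stated power is unsupported for that test

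*Protocol article*

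**What the plan says.** Under Sample size and power analysis, the protocol article states: "A sample of 786 business advisors randomly allocated (1:1) to the two study arms will achieve 80% power". The target difference is d = 0.20, or 1.52 points, on the advisors' relationship-quality score. The standard deviation comes from a validation study "on 408 participants who reported a mean score of 46.36 and standard deviation of 7.60". The test is two-sided at 0.05, and the recruitment target follows from the attrition allowance: "Assuming a 20% attrition rate, we will recruit 984 business advisors". No standard deviation of change and no correlation between baseline and follow-up is given.

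Under Statistics, the terms of the model are fixed: "The GEE model will contain the fixed effect of intervention allocation and nominal time points as the main effects", together with their two-way interaction. The tested quantity is also fixed: "The two-way interaction will estimate the effect of differential change from baseline measure in the intervention compared with control group", with the interaction at 2 months named as the test of the hypothesis. The working correlation is unstructured, with a robust variance. Baseline therefore enters as one of the repeated outcomes, the arm difference at baseline is left free, and no baseline covariate is named.

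**The concern.** The two sections describe different tests. The sample size rests on the spread of a single score, whereas the planned contrast rests on the spread of a change, which depends on how strongly baseline and follow-up are correlated. A power figure for one does not carry over to the other unless that correlation happens to have one particular value.

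Two things are at stake. First, the reader cannot tell what power the planned test has. Second, in a randomised comparison with baseline already collected, the unadjusted difference in change is less precise than a baseline-adjusted comparison of the same people.

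**Working it through.** **Inputs from the protocol article.** Two-sided alpha 0.05; difference 1.52; SD 7.60 (0.20 × 7.60 = 1.52); 393 per arm (786 in total); 20% attrition; 984 recruited (492 per arm). **Assumed:** rho, shown from 0.3 to 0.7 because the article gives none, and equal variance at baseline and follow-up.

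**1. The plan's own figure.** n per arm = 2 × (1.96 + 0.8416)² × (7.60/1.52)² = 2 × 7.849 × 25 = 392.4, so 393 per arm and 786 in total. Power at 393 per arm is 80.06% (normal approximation) or 79.96% (t test). With attrition, 393/0.8 = 491.25, so 492 per arm and 984 in total. Both stated figures reproduce, as a comparison of raw scores at one time point.

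**2. What the planned interaction estimates.** With arm, time and arm-by-time terms and complete data, the interaction is the raw difference between arms in mean change. A GEE with unstructured correlation, fitted to simulated three-visit data with 393 per arm at rho 0.3, 0.5 and 0.7, gave the same estimate as that raw difference to 14 decimals. The unstructured correlation does not turn the contrast into a baseline-adjusted one.

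**3. Standard deviations.**
- Planned: SD of change = 7.60 × √(2(1 − rho)).
- Baseline-adjusted: residual SD = 7.60 × √(1 − rho²).
- Power = Φ(1.52/SE − 1.96), with SE = SD × √(2/393).

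Example at rho 0.3, planned: SD = 8.99, SE = 0.641, 1.52/0.641 − 1.96 = 0.41, power 65.9%.

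**4. Results at 393 complete pairs per arm.**

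| rho (assumed) | Power, planned | Power, adjusted | N for 80%, planned | N for 80%, adjusted | Variance ratio, planned/adjusted = 2/(1 + rho) |
|---|---|---|---|---|---|
| 0.3 | 65.9% | 83.6% | 1100 | 716 | 1.54 |
| 0.4 | 72.6% | 86.4% | 942 | 660 | 1.43 |
| 0.5 | 80.1% | 89.9% | 786 | 590 | 1.33 |
| 0.6 | 88.0% | 93.9% | 628 | 504 | 1.25 |
| 0.7 | 95.1% | 97.5% | 472 | 402 | 1.18 |

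The planned test matches the sized test when 2(1 − rho) = 1, that is rho = 0.5. At rho = 0 the adjusted comparison has the sized power (80.1%), and it rises from there.

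**5. Using the baselines of dropouts.** Suppose all 492 per arm give a baseline and 393 give a follow-up. The variance of the planned contrast per arm is then 7.60² × [(1 − rho²)/393 + (1 − rho)²/492]. Power is 69.1%, 75.2%, 82.0%, 89.2% and 95.7% at rho 0.3, 0.4, 0.5, 0.6 and 0.7. Break-even is 1/(1 + √(492/393)) = 0.47. The first term in the bracket is the variance of the adjusted comparison, so the planned contrast remains the less precise one for every rho below 1.

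**The case against.** **No shortfall is shown.** This stands. A reader might infer that the trial is underpowered, or that 80% strictly requires a correlation of 0.5 or more. The article supports neither. It gives no correlation; above 0.5 the planned test exceeds 80%; and the break-even falls to about 0.47 when dropouts' baselines contribute, which the article's statement that GEE uses all available data allows.

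**The planned analysis is valid.** This also stands. An arm-by-time interaction with robust variance is a standard analysis, and nothing here points to bias or an inflated type I error. The point concerns precision and a power figure attached to the wrong test. It can also be said that change is the question asked. But under randomisation with comparable baselines, both analyses estimate the same arm difference, so adjustment gives up nothing.

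**Baselines may not be comparable.** This stands in part. Under Inclusion criteria, advisors learn their arm after agreeing to take part, and the text shown does not establish that the baseline survey comes first. If it follows disclosure, forcing equal baseline means could be wrong. If real baseline differences arose, adjusted and change analyses would no longer target the same quantity. This limits the form of the remedy. It does not rescue the power statement.

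**The result might be stretched too far.** A reader might extend the gain to SME owners or to every primary outcome. Owners are invited by advisors who have already been randomised, so their baseline equivalence is not secured by the randomisation. Provision of mental health first aid is a binary item plus a count of actions, for which these variance formulas were not derived.

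**It belongs in an analysis plan.** This does not stand. The article itself fixes the model terms, the working correlation, the variance estimator and the tested contrast.

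**Conclusion.** The concern holds, within limits. The 786 is arithmetically right for a single-time-point comparison and does not establish 80% power for the difference in change that will be tested. With 393 complete pairs per arm and an assumed correlation of 0.3 to 0.7, planned power lies between about 66% and 95%, and adjusted power between about 84% and 98%. Planned power is unknown rather than shown to be too low. The loss of precision against baseline adjustment does not depend on the unknown value: it is present at every correlation below 1, with planned variance 1.18 to 1.54 times the adjusted variance over the assumed range. These results rest on equal variances over time, comparable arms at baseline and a continuous score. They are claimed for the advisors' relationship-quality score and other continuous advisor scores only.

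**What to change.** - For the advisors' relationship-quality score, and the other continuous advisor scores, model the 2- and 6-month outcomes with the baseline score as a covariate.
- Constrain the arms to a common baseline mean only if the baseline survey is completed before the arm is disclosed. State which order applies.
- State the assumed baseline-to-follow-up correlation, and restate power at 786 as at least 80% for the adjusted comparison.
- Do not carry the precision claim over to SME owners or to the binary and count outcomes.

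The statistical change is a line of model specification and needs no extra data or participants. The trial is already recruiting, and under Ethical principles amendments go to the ethics committee and the registry, so that administrative step should be counted too.

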### Randomisation

Simple random allocation will be used to ensure the sample size is balanced across the two groups (1:1). Should differential attrition arise part-way through the project, i.e., due to a preference to partake in the intervention, the allocation ratio will be adjusted to compensate for this, i.e., a 1:2 ratio (MHFA+RBT: MHFA). The membership engagement officer at each business advisor’s member organisation (i.e., CAANZ, CPA, IPA, ICB) will conduct the randomisation process by providing eligible participants with a computer-generated unique numeric ID and allocating them to RBT + MHFA or MHFA alone. The participant’s names will be concealed throughout this process. Allocation concealment will be achieved because the member organisations will be unable to predict the unique ID allocated to each participant before they are sorted and randomised to a group. Participants will use their unique ID for completing the surveys, and the researchers will not have access to the business advisor’s contact details only unique ID, group allocation and survey results. Any contact will occur via member bodies or training vendor.

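### Moving to 1:2 allocation to equalise the arms gives no power gain at a fixed total of 984, and pooling the two phases unless a test is significant leaves arm partly tied to period

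*Protocol article*

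**What the plan says.** The Randomisation section starts at 1:1 and says that, if dropout differs between arms during the project, "the allocation ratio will be adjusted to compensate for this, i.e., a 1:2 ratio (MHFA+RBT: MHFA". The Statistics section presents this as a possible pragmatic decision, prompted by expected dropout in the less attractive MHFA-alone arm. Its aim is "to allocate more participants to MHFA alone to have equal number of participants in both groups to enhance statistical power".

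The same section accepts that bias could follow and plans to test the two parts of the trial for homogeneity. The consequence is conditional: "If any significant differences are identified, the results will be analysed separately and then combined, as in a meta-analysis". The GEE model described there contains arm, time point and their interaction, with no term for trial part.

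The Recruitment section closes enrolment at 984 advisors in total. No per-arm attrition, trigger or timing for the switch is given.

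**The concern.** Two things look wrong.

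- **The rationale.** At a fixed total, every extra control participant is one fewer intervention participant, and the extra places go to the arm that loses more people. Equal completers is not the same goal as maximum power.
- **The analysis after a switch.** Controls then come more from the later phase than intervention participants do. If the phases are pooled with no phase term, any difference between phases in change from baseline enters the arm contrast. Recruitment runs for 18 months from February 2021, and the Discussion itself names pandemic lockdowns as something the randomised design should guard against. A constant ratio gives that protection; a changing ratio with an unadjusted analysis weakens it.

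**Working it through.** **Inputs from the article (Sample size and power analysis).** "A sample of 786 business advisors randomly allocated (1:1) to the two study arms will achieve 80% power"; "effect size d = 0.2 in the primary outcome or a mean difference of 1.52 between the two groups"; "mean score of 46.36 and standard deviation of 7.60"; "Calculations are based on a two-tailed test and α = 0.05"; "Assuming a 20% attrition rate, we will recruit 984 business advisors".

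**Assumptions, not in the article.** Retention rI (intervention) and rC (control), shown as ranges, and a switch after half of recruitment.

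**Reproducing the plan's figure.** 1.52/7.60 = 0.20. A two-sided 5% test with 80% power needs 393 per arm, 786 in total (power 80.06%). 393/0.8 = 491.25, rounded up to 492 per arm, gives 984. The stated figures reproduce.

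**Equal completers.** Let k be the control:intervention ratio and N = 984. The variance of the arm difference is proportional to V(k)/N, with

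V(k) = (1+k)(1/rI + 1/(k·rC)).

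- At 1:1, V(1) = 2/rI + 2/rC.
- Completers are equal when k = rI/rC. Then V = (1+k)(2/rI) = 2/rI + 2/rC, the same as 1:1.
- In general V(k) − V(1) = (k−1)[1/rI − 1/(k·rC)], so for k > 1 the switch helps only if rI/rC > k. For k = 2, control retention must be below half of intervention retention.
- The best ratio is k = √(rI/rC), where V = (1/√rI + 1/√rC)². At 80%/60% this is (1.118 + 1.291)² = 5.803, against V(1) = 2(1.250 + 1.667) = 5.833. Effective n per arm, 2N/V, is 1968/5.803 = 339 against 1968/5.833 = 337. Even the ideal ratio gains about 2 per arm.

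**Halfway switch.** Part 1 randomises 246 + 246 and part 2 randomises 164 + 328, so the totals are 410 intervention and 574 control (k = 1.40). Effective n per arm is 2/(1/nI + 1/nC) on completers; analysed by part, the two values are added.

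*Example at 80%/70%.* 1:1: completers 393.6 and 344.4, giving 367. By part: 183.7 + 167.0 = 351. Pooled: 328 and 401.8, giving 361.

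| Retention I/C | 1:1: n (power) | Halfway switch, pooled | Halfway switch, by part |
|---|---|---|---|
| 80%/80% | 394 (80.1%) | 383 (79.0%) | 372 (77.8%) |
| 80%/70% | 367 (77.4%) | 361 (76.7%) | 351 (75.4%) |
| 80%/60% | 337 (73.8%) | 336 (73.6%) | 326 (72.4%) |
| 90%/60% | 354 (75.9%) | 356 (76.1%) | 346 (74.9%) |
| 80%/50% | 303 (69.2%) | 306 (69.7%) | 297 (68.4%) |
| 80%/40% | 262 (63.0%) | 270 (64.2%) | 262 (63.0%) |

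Pooled break-even is at rI/rC = 1.67, 1.40 or 1.18 for a switch after 25%, 50% or 75% of recruitment. By part, break-even is always 2.

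**Link between arm and period.** Part 2 supplies 164/410 = 40.0% of intervention and 328/574 = 57.1% of control participants. A period difference δ in mean change biases the pooled contrast by (0.571 − 0.400)δ. For δ = 0.2 SD this is 0.034 SD, which is 17% of the target d = 0.2, or 0.034 × 7.60 ≈ 0.26 points if the SD of 7.60 applies.

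**Type I error at δ = 0.2 SD.** With 80% retention in both arms, completers are 328 and 459, and SE = √(1/328 + 1/459) = 0.072 SD. The bias is then 0.47 SE. Always pooling gives a two-sided type I error of about 7.6%. Simulating the stated rule (pool unless the test is significant):

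- Test of the period shift in change scores, which has 80% power for 0.2 SD: about 5–6%.
- Test of treatment-by-period interaction, or of baseline characteristics unrelated to the shift: about 7.6%.
- Always analysed by part: about 5%.

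**The case against.** **Power.** A reader might infer that the switch lowers power at any plausible attrition. The article does not support that. It describes a part-way change, with pooling unless the parts differ, and on that analysis a halfway switch is neutral or slightly better once the retention ratio passes 1.40 (303 to 306 at 80%/50%). That objection stands. But the gain is at most about a point in the scenarios tabulated, and it comes from comparing people across phases, which is the comparison exposed to period effects. Analysed by part, the same switch loses power at 80%/50%. If controls were added beyond 984, power would rise because the trial was larger, not because of the ratio.

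**Two harms at once.** It is also tempting to quote the power loss and the type I inflation together. They belong to different analyses: the loss to analysis by part, the inflation to pooling. One analysis does not suffer both.

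**The safeguard.** A reader might take 7.6%, or about 11% at a 0.3 SD shift, as the expected type I error. Those are the always-pooled figures, whereas the article tests first. If that test covers change scores, it detects a 0.2 SD shift with 80% power and a 0.3 SD shift about 99% of the time, and the inflation is under one point. A low power of about 29% to detect a 0.2 SD treatment-by-period difference is beside the point, because the bias arises from a period shift common to both arms. Against this, the article's reason for testing is that participants may differ in important characteristics, and it does not name the data tested. The protection cannot be assumed.

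**Extent.** The association is partial (40% against 57%), stable differences between phases cancel in the arm-by-time interaction, and the article acknowledges the risk. All of this stands and limits the severity. It is nevertheless a rule stated in the text, not detail left to an analysis plan.

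**Conclusion.** The point holds in limited form. The stated reason for the switch is wrong: at a fixed 984, equalising completers leaves power exactly where 1:1 has it, whatever the retention. A 1:2 ratio throughout, or any switch analysed by part, costs power unless control retention is below half of intervention retention. With a halfway switch analysed by part the cost is about 1 to 2 points over most of the range shown; analysed pooled, the switch is roughly neutral.

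The conditional pooling rule is the second weakness. It leaves a possible bias of 0.034 SD for a 0.2 SD period difference in change, with type I error between about 5–6% and 7.6% depending on an unstated choice of test.

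These sizes rest on assumed per-arm retention, an assumed halfway switch, an assumed period difference, and the same cross-sectional d = 0.2 that the article uses. Severity is minor to moderate.

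**What to change.** Remove the claim that the ratio change enhances power, and keep 1:1 throughout. If the ratio has been or will be changed, always stratify by allocation phase: add phase and phase-by-time terms to the GEE model, or combine within-phase estimates, whatever the homogeneity test shows. The test can stay as a description, but should not choose the analysis.

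Cost: keeping 1:1 deletes one rule and accepts slightly unequal completers, with negligible effect on power. Stratifying after a switch adds phase terms to the model and gives up about 1 to 2 points of power.
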